### Recruitment

#### Feasibility of recruitment

Participants will be recruited from the Comprehensive Integrated Pain Program – Interventional Pain Service (CIPP-IPS) clinic at TWH or Wasser Pain Clinic at Sinai Health System (both in Toronto, Ontario, Canada). About 100 patients with CDH are treated in these centers each year, out of which 75 are likely to be eligible for participation in this trial. The trial will be discussed with all eligible participants. It is expected that 50% of all eligible participants (37 over 12 months) would consent to participate. Therefore, it is estimated that the enrollment of 56 participants for this trial will be completed in 18 months.

#### Recruitment strategy

The primary investigator will introduce this trial to pain physicians and neurologists who refer patients with CDH to the two trial sites. They will be encouraged to consider referring patients with CDH eligible for this trial.

## Assignment of interventions

### Randomization, sequence generation, and allocation concealment

Upon participant enrollment, patients will be randomized to one of two arms, with a 1:1 allocation and random permuted blocks of six. The randomization sequence will be computer generated by a member of the research team. The treatment allocation will be performed by an independent research coordinator not otherwise involved in the study, who will ensure allocation concealment by sequentially numbered, sealed opaque envelopes. This allocation sequence will be provided to the unblinded pharmacist

### Blinding

#### Blinding mechanism

A delegated unblinded healthcare provider with the appropriate qualifications will retrieve the trial medication of the unblinded pharmacist and prepare the trial medication. This healthcare provider will provide it to the blinded physician and blinded research team on the day of infusion. Participants, physicians, and all outcome assessors will all be blinded during the conduct of the trial and statistical analysis. Ketamine and saline are both clear liquids with no discernable smell. The use of IV midazolam during the infusion, which generates a sedated but arousable state (Ramsay Sedation Scale score of 3 or 4) [19] will increase the probability of blinding the participants and outcome assessors to group allocation.

#### Emergency unblinding

Emergency unblinding will only occur when knowledge of the intervention is essential for patient care as determined by the principal investigator or the Data Safety Monitoring Board. In the event of emergency unblinding, the timing, reason, and personnel involved will be recorded in the CRF, and blinding will be maintained in as many other trial personnel as possible.

## Data collection

### Data collection methods

All data will be collected on paper case record forms and then entered manually by trial personnel in duplicate, into a pilot-tested, password-protected, electronic database (Microsoft Excel platform).

Our data collectors are experienced research assistants who have been trained in Good Clinical Practice (GCP). There will be regular meetings between the data collectors and the trial principal investigator involved. We will use validated questionnaires for assessing pain and related domains. Patients will be followed closely at dedicated time points to promote retention and complete follow-up.

#### Baseline data

Data captured at baseline will include demographic information (patient age, gender, height, weight, comorbidities), headache-related information (type of headache, duration of pain, duration, and number of headache days and intensity in 28 days before infusion), vital signs (heart rate, blood pressure), medication and analgesic intake, quality of sleep, mood, and activity.

#### Infusion data

Data captured during and immediately after the infusion will include the intensity of headache (NRS), global improvement (PGIC), and adverse effects (Bowdle, CADSS)

#### Follow-up data

Data will be captured at 28, 56, and 84 days after the infusions and data will also be collected by the actigraphy device for the first 28 days after the infusion.

### Data management and confidentiality

All trial data will be checked for errors and missing data on a regular basis. Trial data from the actigraphy device and the app will be exported as a comma-separated values (CSV) file for analysis. It will be locally synced on an institutional research laptop. Participants’ contact information and identifying information will be encrypted and stored in a separate database. Identifying information will be deleted once follow-up is completed. The Institutional Research Ethics Board (IREB) audits trial records and collected personal health information to verify that the information collected for the trial is correct and to make sure the trial is following institutional regulations.

Completed questionnaires collected during the trial visits will be labeled with a unique trial code. No patient names will be used. The information that links the unique trial code to the participant will be kept in a secure area in our institute, and it will be distinct from the participants’ trial data. This information can only be accessed by research team members who are involved in the trial.

All records and documents pertaining to the trial will be retained by the trial sites for 25 years from the completion of the trial, as per Health Canada regulations.

In the event of personal health information disclosure to an unauthorized party, the following will be done: any further release of information will be stopped, as much information as possible will be retrieved, IREB privacy Offices will be contacted, and further actions would be taken based on their recommendations.

### Statistical methods

The normality of the trial data will be assessed, means and standard deviation (or median and interquartile ranges, as appropriate) will be used to summarize continuous data, and frequencies and proportions will be used for categorical data. To compare data between the 2 groups, categorical outcomes will be analyzed with the chi-square test and continuous variables will be analyzed with independent *t*-tests (or Wilcoxon rank sum test). A baseline-adjusted ANCOVA model will be employed for all outcome variables of interest for which a baseline is recorded in the 28 days interval prior to treatment. In addition, for the primary outcome, an additional ANCOVA model will be employed adjusting for baseline headache days and the following variables that are strongly associated with this outcome: number of headache years, depression/anxiety, intensity of headache, and opioid intake. Estimates of differences in means (with 95% CI) at 28, 56, and 84 days will be provided for continuous outcomes. A Cox proportional hazards model will be built to investigate the effect on variables on the time to a specified event. Missing primary outcome data will not be imputed. A sensitivity analysis assuming the participants lost to follow-up showed no improvement (i.e., they had no change in headache frequency) will then be performed. Group comparisons will be performed in responders (defined as a reduction in pain by 3 or more headache days in 28 days from baseline at 28 days after the infusions) versus non-responders, participants on Botox/CGRP antagonist treatment versus none, comparison across different subtype of CDH, and baseline frequency and average intensity of headaches. An intention-to-treat analysis approach will be used. SAS Studio Edition will be used to conduct the analyses.

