#### Secondary outcomes

Number of headache days in periods from 29 to 56 days and 57 to 84 days after the infusion; the between-group difference in the number of headache days from 29 to 56 days and 57 to 84 days after the infusion.

The following will be assessed at baseline and from 1 to 28 days, 29 to 56 days, and 57 to 84 days after the infusion:Pain intensity: average intensity of headaches as measured on an 11-point Numerical Rating Scale (NRS; 0–10) [20]. During the trial, participants will be asked to rate their daily average pain level in a diary. The baseline headache intensity will be calculated as the mean of the daily pain score in the 28 days before the trial infusion.Duration of headache episodes: the duration of the (daily) headache will be measured in hours in the pain diary. The baseline headache duration will be calculated as the mean of the duration of daily headaches in the 28 days before the trial infusion.Time until the new onset of headache: determine the average number of days until the recurrence of headache after the trial infusion.Sleep duration and quality: average daily duration of sleep as measured by the actigraphy wearable device (for 28 days after the infusion).Sleep quality: quality of sleep as measured by the Pittsburgh Sleep Quality Index (PSQI) [21].Physical activity: average daily physical activity as measured by the actigraphy wearable device (at 28 days after the infusion) and Brief Pain Inventory (BPI) [22].Functioning: impact of headaches on functioning as measured by the Headache Impact Test (HIT-6) [23] score and Migraine Disability Assessment (MIDAS) [24].Psychological health: emotional function as measured by Generalized Anxiety Disorder-7 items (GAD-7) [25], Pain Catastrophizing Scale (PCS) [26], and Patient Health Questionnaire for Depression-9 items (PHQ-9) [27] instruments.Quality of life: health-related quality of life measured by EuroQol-5 dimensions, 5-item questionnaire (EQ-5D-5L) [28].Participant satisfaction: participant satisfaction as measured by the Participant Global Impression of Change (PGIC) [29].Adverse effects: adverse effects of ketamine as measured on the Clinician-Administered Dissociative States Scale (CADSS) [30] and Bowdle [31] questionnaires at end of the infusion.Analgesic consumption: analgesic consumption will be measured by intake frequency and doses of headache-specific (abortive and prophylactic) medication and average daily oral morphine equivalent (OME) in milligrams.

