### Sample size

A difference of 3 headache days (standard deviation (SD) of 3.8) in the frequency of headache days between the two groups in the 28 days after the trial infusion is considered as a minimum clinically important difference (MCID) [32] for this trial. A sample size of 25 participants in each group would have over 80% power to detect this difference between the 2 groups using a two-sided alpha of 0.05. Assuming a 10% drop-out rate 1 month after the infusions, 28 participants will be enrolled in each arm. This sample size is also robust to capture a key secondary outcome for this trial—a MCID of 1.0 (SD 1.3) in the mean 0–10 NRS score for average intensity of headaches in the first 28 days after the infusions (power of over 80% with a two-sided alpha 0.05) [14].

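### On its plainest reading, the protocol's two-way test rule sends the ordered Global Impression of Change (PGIC) to a chi-square test that ignores order; a test that uses the order should be named (minor)

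*Protocol article*

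**What the plan says.** The Statistical methods section of the protocol article sorts between-arm comparisons by data type: "categorical outcomes will be analyzed with the chi-square test and continuous variables will be analyzed with independent" t-tests. The rank test appears only in parentheses after the t-test, "or Wilcoxon rank sum test", and so belongs to continuous variables. No method is named for ordered categories. Baseline-adjusted ANCOVA is added for outcomes that have a value recorded in the 28 days before treatment. Differences in means with 95% CIs are promised for continuous outcomes.

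The Secondary outcomes section lists "participant satisfaction as measured by the Participant Global Impression of Change (PGIC"). The Objectives include participants' impression of change at days 28, 56 and 84. The Infusion data section also collects "global improvement (PGIC), and adverse effects (Bowdle, CADSS") around the end of the infusion. The article does not give the number of PGIC levels, say whether PGIC counts as categorical or continuous, or name its test.

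**The concern.** A rating of change runs from worse to better. If it is treated as categorical, the only test the article offers is Pearson's chi-square, whose value does not alter when the categories are reordered. It asks whether the two patterns differ in any way and spends one degree of freedom on each category beyond the first. The clinical question is whether ratings lie further towards improvement on ketamine.

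Two other routes in the text do not clearly rescue PGIC:

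- **ANCOVA** needs a pre-infusion value. The lead-in to the secondary outcomes nominally includes PGIC among items assessed at baseline. But a rating of change has no meaningful value before treatment, and the Baseline data section lists no global impression.
- **Dichotomising** is not mentioned for PGIC. The responder definition in Statistical methods rests on headache days.

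At stake is a real shift in one secondary outcome being missed more often than necessary in a small trial. As a categorical outcome, PGIC would also have no promised effect estimate with a confidence interval.

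**Working it through.** **Inputs from the Sample size section.** "A sample size of 25 participants in each group would have over 80% power to detect this difference", "using a two-sided alpha of 0.05". The primary effect is 3 days with SD 3.8, so 3/3.8 = 0.79. The key secondary effect (NRS intensity) is 1.0 with SD 1.3, so 1.0/1.3 = 0.77.

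**The plan's own figure.** Normal-approximation power is Φ(d·√(n/2) − 1.96). With d = 0.789 and n = 25, 0.789 × 3.536 − 1.96 = 0.83, and Φ(0.83) = 79.7% (78.1% with the noncentral t). This matches the stated figure to rounding. Allowing for drop-out, 25/0.9 = 27.8, so 28 per arm, as stated. No power or effect size is stated for PGIC.

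**Assumptions added here.** PGIC has 3, 5 or 7 levels. The treatment effect is a uniform shift on a normal latent scale, equal to the plan's standardised effects. Several category patterns, even and peaked, were tried. Pearson chi-square was compared with the tie-corrected Wilcoxon test at 25 per arm and two-sided 0.05, with 6,000 to 20,000 simulated trials per setting.

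| Levels | Shift (SD) | Chi-square power | Wilcoxon power | Loss (points) |
|---|---|---|---|---|
| 3 | 0.79 | 55–58% | 67–68% | 10–12 |
| 5 | 0.79 | 46–49% | 72–73% | 23–26 |
| 7 | 0.79 | 31–43% | 70–75% | 31–41 |
| 3 | 0.77 | 54% | 66% | 12 |
| 5 | 0.77 | 44–47% | 70–71% | 23–27 |
| 7 | 0.77 | 30–40% | 70–72% | 31–40 |

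**Closed-form cross-check.** Suppose a 1-df ordered test has 70% power. Its noncentrality is (1.960 + 0.524)² = 6.17. The same noncentrality spread over 2, 4 and 6 df (3, 5 and 7 levels) gives 59.7%, 48.2% and 41.4%, so losses of 10, 22 and 29 points. Starting from 80%, the figures are 70.9%, 59.5% and 52.1%, so losses of 9, 20 and 28 points. The order of magnitude agrees with the simulation.

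**Where the loss shrinks, vanishes or reverses (25 per arm).**

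- At a 0.3 SD shift the loss is about 3 points with 3 levels (12.2% against 15.0%), 8 with 5 levels (8.6% against 16.6%), and 8 to 11 with 7 levels.
- If PGIC is dichotomised, the two tests coincide: 63% each at 0.79 SD.
- If treatment spreads ratings in both directions, chi-square wins, for example 74% against 16%.

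**Sparse cells.** With evenly used categories, the expected count per cell is 25/5 = 5.0 at 5 levels and 25/7 = 3.6 at 7. Across the 7-level patterns, about two thirds to four fifths of cells fall below 5. Even so, chi-square type I error stayed at 3.5–5.2%, so sparseness does not inflate false positives under these assumptions.

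**The case against.** The strongest reply is that the article never classes PGIC as categorical. It handles another rating scale, the 0–10 NRS, through means and SDs, and PGIC stands in the same list of instruments. Treated as a score, it would go to the t-test or Wilcoxon test, and Wilcoxon is the very remedy proposed here. Chi-square also has natural uses elsewhere, such as prevalence of adverse effects. Choosing a test for each outcome is commonly left to an analysis plan, which is not shown, so its absence from this article is no fault.

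Much of this stands. A reader might infer that the plan has committed itself to chi-square for PGIC at a known cost in power. The article supports neither part: the classification is an inference, and the size of the loss rests on levels, distribution and effect that it does not give. A reader might also infer that a significant chi-square result would leave the direction unknown. That goes too far, because frequencies and proportions will be reported. Finally, the secondary hypotheses do not name impression of change, and the Sample size section singles out NRS intensity as the key secondary outcome.

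What the reply does not remove is the rule as written. It has two branches, the rank test sits in the continuous branch only, and an ordered rating of change fits the other branch more naturally. Under the more favourable reading, the choice between an ordered and an unordered test is still not settled by this text.

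**Conclusion.** The point holds as a minor one. As worded, the rule most naturally sends PGIC to a test that ignores order. With 25 per arm, 3 to 7 levels and a uniform shift of 0.77 to 0.79 SD, this would cost roughly 10 to 40 points of power, most with 7 levels. Those shifts are borrowed from headache days and NRS intensity, so the range is conditional and not a property of the plan. It falls to about 3 to 11 points at 0.3 SD, to zero if PGIC is dichotomised, and can change sign if the effect is not a shift. The primary analysis, the sample size and the validity of the type I error are not in question.

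**What to change.** In Statistical methods, limit the chi-square test to binary or unordered outcomes. Add that ordered categorical outcomes, such as PGIC at the end of infusion and at days 28, 56 and 84, are compared with the tie-corrected Wilcoxon rank-sum test or a proportional-odds model. Report an effect estimate with 95% CI: the probability of a better rating, or the common odds ratio.

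The cost is one sentence, with no new data, visits or participants. The small downside is less sensitivity to a difference in spread without a shift. Full frequency tables by arm, which the plan already provides for, would still show such a pattern.

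### Days 29–56 and 57–84 are compared without the same participants' earlier post-infusion data, so these secondary estimates may be biased, in a direction that depends on who leaves each arm

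*Protocol article*

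**What the plan says.** The Statistical methods section names an independent t-test or Wilcoxon rank sum test for continuous variables and adds: "A baseline-adjusted ANCOVA model will be employed for all outcome variables of interest for which a baseline is recorded in the 28 days interval". Results are then promised by time point: "Estimates of differences in means (with 95% CI) at 28, 56, and 84 days will be provided for continuous outcomes". The primary outcome gets one further ANCOVA. All its extra covariates are patient characteristics or headache history. No mixed model, GEE or other longitudinal method appears, and no post-infusion value is named as a covariate.

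On missing data, the section rules out imputation for the primary outcome and says nothing about the secondary outcomes. It adds one sensitivity analysis in which participants lost to follow-up are taken to have unchanged headache frequency.

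The Sample size section gives the only loss rate: "Assuming a 10% drop-out rate 1 month after the infusions, 28 participants will be enrolled in each arm". No rate is given for day 56 or day 84.

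**The concern.** Headache days, intensity and duration are recorded in the same people in three consecutive 28-day windows, and most questionnaires follow the same schedule. The later windows show whether a single infusion has a lasting effect, which is the aim of the 84-day follow-up.

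A participant who completes the diary for days 1–28 and then leaves contributes nothing to a separate ANCOVA for days 29–56 or 57–84, although the first window helps to predict the later ones. Such an ANCOVA is safe if loss depends only on arm and baseline. After a single infusion, loss could also depend on how the participant has fared since. The protocol has exit routes that may differ by arm: the Modifications section ends participation after a serious adverse event, and the withdrawal criteria let the investigator remove participants for adverse events or non-compliance. At stake is the accuracy of the durability estimates, and some collected data that would go unused.

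**Working it through.** **1. The plan's own figure.** Inputs from the Sample size section: difference 3 days, SD 3.8, two-sided alpha 0.05.

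- n per group = 2(1.960 + 0.842)² × (3.8/3)² = 2 × 7.849 × 1.604 = 25.2, so 26 against the stated 25.
- Power with 25: 3/(3.8 × √(2/25)) = 2.791; 2.791 − 1.960 = 0.831, giving 79.7% (78.1% with the noncentral t).
- Enrolment: 25/0.9 = 27.8, so 28 per arm.

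The figure reproduces to within one participant per group, although power falls just short of the claimed 80%. This point does not bear on it.

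**2. Why separate ANCOVA can be biased, and which way.** Let δ be the shift, among those who stay in an arm, in the earlier post-infusion value after adjustment for baseline. Let β be the slope of the later value on that earlier value. The later arm difference (ketamine minus placebo) is then off by about β(δ_ketamine − δ_placebo). Losing poor responders makes δ negative, because those who stay have fewer headache days. If placebo loses more of them, the error is positive and a true −3 moves toward zero. If ketamine loses more, it moves away from zero. If the two shifts are equal, there is no error.

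**3. Size.** None of the following inputs is in the protocol, apart from the SD of 3.8 and the 3-day difference. Assumptions:

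- true effect −3 days in every window;
- correlation 0.5 or 0.7, either AR(1) or exchangeable;
- 10% or 20% lost after each of the first two windows, so 0.9² = 81% or 0.8² = 64% remain at days 57–84;
- loss driven by change from baseline, with logistic slope 1 or 2 per SD (slope 1 in the one-arm scenarios);
- 400,000 simulated participants per scenario, so that sampling error is negligible.

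| Who leaves | Loss per window | ANCOVA, day 56 | ANCOVA, day 84 |
|---|---|---|---|
| At random | 10% | −2.98 to −3.01 | −2.99 to −3.02 |
| Poor responders, same mechanism in both arms | 10% | −2.80 to −2.95 | −2.63 to −2.92 |
| Same | 20% | −2.66 to −2.92 | −2.44 to −2.86 |
| Poor responders, placebo only | 10% | −2.85 to −2.92 | −2.70 to −2.83 |
| Poor responders, ketamine only | 10% | −3.06 to −3.11 | −3.11 to −3.20 |
| Same | 20% | −3.10 to −3.21 | −3.21 to −3.39 |

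An estimate using all earlier windows gave −2.97 to −3.02 at days 56 and 84 in every scenario.

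The same-mechanism rows shrink because placebo has more poor responders to lose: at 10% per window, 72–76% of placebo and 86–90% of ketamine participants remain by day 84.

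The unadjusted t-test at day 84 (same mechanism, 10%) is off by 0.09 to 0.23 days under AR(1). Under exchangeable correlation it is essentially unbiased, because change from baseline is then uncorrelated with the later value (ρ − ρ = 0).

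**4. Against the standard error.** With 28 × 0.81 = 22.7 per arm, the standard error is 3.8 × √(2/22.7) × √(1 − r²) = 1.128 × √(1 − r²), where r is the correlation of baseline with the last window.

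- Largest same-mechanism bias at 10%: AR(1) with ρ = 0.7, r = 0.7³ = 0.343, standard error 1.06; 0.37/1.06 = 0.35.
- Smallest: exchangeable 0.7, standard error 0.81; 0.08/0.81 = 0.10.

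**5. Trial-sized check.** A separate simulation used 28 per arm, 1,500 trials per scenario, correlations of 0.6 to 0.85 between adjacent windows, about 20% lost by day 84, and loss depending on the preceding window. Day-84 ANCOVA gave 2.68–2.86 for a true 3.0. A repeated-measures likelihood model gave 2.96–3.01, with a standard error equal or up to about 6% smaller.

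**The case against.** The strongest objections, and what remains of each:

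- **Direction.** A reader might infer that the planned analysis shrinks the later effects toward zero. The documents do not support that as a general statement. They do not say who will leave which arm, and the sign reverses if poor responders leave mainly from ketamine. This objection stands in full.
- **Missing secondary data.** A reader might also take an observed-cases rule as stated for every outcome. The protocol rules out imputation for the primary outcome only. For the rest, the rule is inferred from the named methods, and the full protocol or analysis plan may say more. What does not depend on that inference is that the stated comparisons use no earlier post-infusion data.
- **The no-change sensitivity analysis.** It does address poor responders who leave. But it covers headache frequency only and imposes a single value. If applied to the later windows, it would override an improvement already observed in days 1–28.
- **Assumed loss.** The correlations and the loss after day 28 are assumptions. Virtual or telephone visits and close follow-up may keep loss low, and with little loss the bias is small.
- **Accepted method and bounded counts.** ANCOVA per window is an accepted analysis, and headache days cannot exceed 28 per window. But the plan already commits to mean differences from a normal-theory ANCOVA, so the mixed model adds little on that score. What it adds is reliance on missing at random, which is weaker than requiring loss to depend on arm and baseline alone.

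**Conclusion.** The point holds for the secondary windows. As stated, the comparisons for days 29–56 and 57–84 leave out the same participants' earlier post-infusion data. They may be biased if loss depends on earlier response, in a direction that depends on who leaves each arm.

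At 10% loss per window the day-84 ANCOVA is off by 0.08 to 0.37 days toward no effect under a common mechanism, and by 0.11 to 0.20 days away from it if only ketamine loses poor responders. With random loss there is no bias, and the gain from the alternative is a little precision. All these sizes rest on assumed correlations and loss.

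It would be wrong to read this as a threat to the primary result: days 1–28 have no earlier post-infusion window to borrow from, and the sample size is untouched. The grade is a cheap improvement, minor to should-fix.

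**What to change.** For each continuous outcome measured at 28, 56 and 84 days, fit one mixed model for repeated measures with arm, window, arm-by-window, baseline and baseline-by-window, unstructured covariance and Kenward-Roger degrees of freedom. Report the arm difference with 95% CI in each window from this model. Keep the no-change analysis and the Wilcoxon test as sensitivity analyses. With complete data the day-28 contrast matches the ANCOVA already planned.

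The cost is a change of analysis wording and one procedure in the SAS software already named. No new data or participants are needed. The model relies on missing at random and approximate normality, and it estimates six covariance parameters (three variances, three covariances) in 56 participants, which is feasible.

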### Outcomes

#### Primary clinical outcome

The between-group difference in the number of headache days in the first 28 days after the infusion is the primary outcome of this trial. A headache day is defined as a day in which the headache lasts 4 or more hours or a headache of any duration for which abortive treatment (anti-inflammatories, triptans, ergot derivatives, opioids) is taken. During the trial, participants will be asked to keep track of their headache days in a diary.

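### Responder status at 28 days, a cut of the primary outcome, is listed among baseline factors for group comparisons; comparing arms within it is not a randomised comparison.

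*Protocol article*

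**What the plan says.** The Statistical methods section of the protocol article states: "Group comparisons will be performed in responders (defined as a reduction in pain by 3 or more headache days", continuing "in 28 days from baseline at 28 days after the infusions) versus non-responders". The same sentence then adds "participants on Botox/CGRP antagonist treatment versus none, comparison across different subtype of CDH, and baseline frequency and average intensity of headaches". Shortly after comes "An intention-to-treat analysis approach will be used".

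Under Primary clinical outcome, the article says: "The between-group difference in the number of headache days in the first 28 days after the infusion is the primary outcome of this trial". The Sample size section supplies the planning figures: "A difference of 3 headache days (standard deviation (SD) of 3.8) in the frequency of headache days between the two groups", and "A sample size of 25 participants in each group would have over 80% power to detect this difference".

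Neither the objectives nor the outcome sections list a responder rate. The sentence in Statistical methods is the only place where responder status appears, and it does not name the outcome to be compared.

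**The concern.** The other members of the list (Botox or CGRP antagonist use, CDH subtype, baseline frequency and intensity) describe participants before treatment. Responder status does not. It is computed from the same 28-day diary as the primary outcome and is affected by treatment if the treatment works. If it serves as a stratum for comparing ketamine with placebo, two things follow:

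- **Comparability is lost.** Placebo participants who improve by 3 or more days are a more selected group than ketamine participants who do so. Randomisation no longer balances the arms within the stratum.
- **The difference shrinks.** Both arms are cut at the same amount of change, so part of any real difference is used up in deciding who falls on which side of the cut.

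At stake is a reported difference among responders, or among non-responders, that a reader would take for a treatment effect. The interpretable quantity, the proportion responding in each arm, is not clearly promised. The definition also speaks of pain while counting headache days.

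**Working it through.** **Inputs.** From the protocol article: difference 3 headache days, SD 3.8, 25 evaluable per group, responder cut 3 days. Assumed here: the mean placebo reduction, the baseline to follow-up correlation, normality, and (in step 2) an SD of 3.8 for the change score.

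**1. The plan's own figure.** n per group = 2(1.96 + 0.8416)² × 3.8² / 3² = 25.2, so 26 against the stated 25. Power at 25 is 79.7% by the normal formula and 78.1% by noncentral t, marginally below the claim but close. The inputs are therefore usable, and nothing below depends on that small gap.

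**2. If change scores are compared.** Let D be the reduction, normal with mean m and SD s, and let a = (3 − m)/s. Then
- P(response) = 1 − Φ(a)
- mean of D in responders = m + s·φ(a)/P
- mean of D in non-responders = m − s·φ(a)/(1 − P)

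With s = 3.8, placebo m = 2 and ketamine m = 5:

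| | Placebo | Ketamine | Difference |
|---|---|---|---|
| a | 0.263 | −0.526 | |
| P(response) | 0.396 | 0.701 | 0.305 |
| Mean D, responders | 2 + 3.8 × 0.3854/0.3962 = 5.70 | 5 + 3.8 × 0.3473/0.7007 = 6.88 | 1.19 |
| Mean D, non-responders | 2 − 3.8 × 0.3854/0.6038 = −0.43 | 5 − 3.8 × 0.3473/0.2993 = 0.59 | 1.02 |

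With the mean placebo reduction varied from 0 to 4 days, the difference runs from 0.87 up to 1.6 days in responders and from 1.38 down to 0.74 days in non-responders. The true value is 3.0 throughout.

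**3. If follow-up counts are compared.** This is closer to the stated primary outcome. Let baseline B and follow-up F each have SD 3.8 with correlation ρ, and D = B − F. The slope of F on D is −(1 − ρ)s² / [2(1 − ρ)s²] = −1/2. If δ is the within-stratum difference in change, the within-stratum difference in counts is 3 − (3 − δ)/2 = 1.5 + δ/2.
- At ρ = 0.5 the SD of D is 3.8 × √(2 × 0.5) = 3.8, so step 2 applies directly: 1.5 + 1.19/2 = 2.09 and 1.5 + 1.02/2 = 2.01 days.
- For ρ from 0.3 to 0.7 and a placebo reduction of 1 or 2 days, the result is 2.0 to 2.1 days.
- Simulating whole-day counts limited to 0 to 28, with an assumed mean baseline of 21 days, gives 1.9 to 2.1. Also forcing every baseline count to at least 15 days (a further assumption) gives 1.6 to 2.1.

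**4. Balance.** Take a prognostic covariate with an assumed correlation of 0.6 with the change, placebo m = 1 and ketamine m = 4. Its mean among responders is 0.6·φ(a)/P: 0.6 × 0.3473/0.2993 = 0.70 SD on placebo and 0.6 × 0.3854/0.6038 = 0.38 SD on ketamine. Before the split, both means are zero.

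**5. Size of the strata.** In the step 2 base case with 25 evaluable per arm, responders number about 0.396 × 25 = 10 on placebo and 0.701 × 25 = 18 on ketamine. The distorted estimate would also be imprecise.

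**The case against.** The best defence is that the sentence is loose and has a valid reading. The same section summarises categorical data by proportions and assigns them the chi-square test, so responders versus non-responders could simply be a binary outcome compared between arms. It could also be a descriptive contrast of those who improved with those who did not, which is an ordinary exercise that claims no treatment effect. Both readings are possible, and it cannot be said with certainty that an invalid analysis is intended. But the text speaks of comparisons performed in responders, and everything else in the list is a baseline grouping factor. Neither benign reading is stated, so the sentence needs an edit on any reading.

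A reader might go further in three ways that the article does not support:

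- **That only about a third of the effect would remain.** This needs the change score to be the variable compared and its SD to be 3.8. The Sample size section attaches 3.8 to the frequency of headache days, and the primary outcome is a count. For counts, roughly two thirds remains (somewhat less if baseline counts are floored). If sleep, mood or quality of life were compared, none of these figures would apply.
- **That the trial's main conclusion is at risk.** The primary t-test or baseline-adjusted ANCOVA is untouched, and no objective, hypothesis or sample size rests on the responder split.
- **That the baseline subgroups are faulty because interaction tests or an exploratory label are not mentioned.** Such detail may sit in an analysis plan that is not shown.

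**Conclusion.** The point holds at moderate severity. As worded, the plan places a post-treatment cut of the primary outcome among the factors for group comparisons. Comparing arms within those strata does not estimate the treatment effect. In every scenario worked here it falls short of the true 3 days: about 1.9 to 2.1 days for follow-up counts (assumed correlation 0.3 to 0.7, placebo reduction 1 to 2 days; as low as 1.6 with a baseline floor of 15 days), and about 0.7 to 1.6 days for change scores with an assumed SD of 3.8 (placebo reduction 0 to 4 days). The size depends on these assumptions. The loss of randomised comparability does not, provided that treatment affects response. Confidence that this is the intended analysis is moderate, because the wording allows other readings. Only a supplementary analysis is affected.

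**What to change.** In Statistical methods:

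- Remove responder status as a stratum for group comparisons.
- Define it as a binary outcome: a reduction of at least 3 headache days from the 28-day baseline to days 1 to 28. Report the proportion in each arm with a risk difference and 95% CI, under the intention-to-treat approach already stated. The planned sensitivity analysis for losses carries over directly, since no change in frequency means non-response.
- Restrict the subgroup comparisons to the baseline factors already listed.
- Word the responder definition in terms of headache days, not pain.
- If a descriptive contrast of responders with non-responders is also wanted, say so and state that it is not a comparison of treatments.

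The cost is a change of wording. Baseline and follow-up diaries already supply the data.
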